# Physical activity and nutrition intervention for Singaporean women aged 50 years and above: study protocol for a randomised controlled trial

**DOI:** 10.1186/s13063-018-2562-2

**Published:** 2018-04-27

**Keywords:** Community - based, Healthy ageing, Intervention, Nutrition, Older women, Physical activity, Randomised controlled trial

## Abstract

**Background:**

The majority of the older Singaporean women aged 50 years and above are physically inactive and have unhealthy dietary habits, placing them at ‘high risk’ of non-communicable diseases (NCDs). The adoption of regular physical activity (PA) and a healthy diet are essential lifestyle behaviours to reduce this risk. This randomised controlled trial (RCT) involves the development, implementation and evaluation of a PA and nutrition programme for community-dwelling Singaporean women who currently attend recreational centres (RCs are public facilities supporting social leisure activities) in their local area. The intervention will be developed after conducting formative evaluation with RC attendees and managers through focus group discussions and pilot testing of resources (i.e. surveys, accelerometers, and health booklets). Programme ambassadors (trained, certified fitness instructors and nutritionists) will deliver all sessions in English and Mandarin; implement classes to meet participants’ varying needs; and conduct sessions at different times at convenient venues. Social Cognitive Theory (SCT) has been selected as the theoretical framework to inform intervention strategies as it explores the interactions of human behaviour with the environment and has been found to be valuable when developing behavioural change interventions particularly in older adults (J Gerontol B Psychol Sci Soc Sci 67B(1):18–26, 2012; Obesity Reviews 15(12):983–95, 2014). Its major construct, self-efficacy, is invaluable in achieving successful behaviour change, such as increasing levels of PA or improving dietary intake (Trials. 2017; 10.1186/s13063-016-1771-9; Psychol Health Med 18(6):714–24, 2013).

**Methods:**

The development and implementation of the PA and nutrition intervention strategies will be guided by SCT and Motivational interviewing (MI) and implemented by trained programme ambassadors at the RCs. Sixty RCs located in Singapore will be selected from five major geographical districts and randomly allocated to the intervention (*n* = 30) or control (*n* = 30) cluster. A sample of 600 (intervention *n* = 300; control *n* = 300) women aged 50 years and above will then be recruited from these 60 centres and only the intervention group will be enrolled into the PA and nutrition intervention. It is hypothesised that by the end of the intervention, the intervention group participants compared to the control group will show significantly greater improvements in the following outcome variables: PA and dietary behaviours, health-related quality of life, objective measures of PA, anthropometric, lipid and glucose profiles. Data will be collected at baseline and 6 months and analysed using mixed regression models.

**Discussion:**

It is anticipated that recruitment, retention and compliance of participants will be challenging due to the target group being unfamiliar with such community-based research programmes.

**Trial registration:**

Australian and New Zealand Clinical Trials Registry, ACTRN12617001022358. Registered on 14 July 2017. https://www.anzctr.org.au/Trial/Registration/TrialReview.aspx?id=372984&isReview=true

**Electronic supplementary material:**

The online version of this article (10.1186/s13063-018-2562-2) contains supplementary material, which is available to authorized users.

## Background

Singapore is a densely populated city with 5.6 million residents, comprising an ethnically diverse population of Chinese (74%), Malay (13%) and Indians (9%) [1], of which the proportion of dependent older adults is growing, representing a challenge for the health sector [2]. Compared to men, Singaporean women have a longer life expectancy [3]. They also have an increased risk of non-communicable diseases (NCDs), especially for those women aged 45 years and above [4]. Older women have been identified as a priority group to target in reducing the risk factors for all NCDs as the prevalence of high blood pressure (BP), cholesterol and diabetes (type 2) rise sharply for women from their 30s into their 60s [5]. In addition, compared to men, women living in Singapore aged 50 to 69 years have higher levels of abdominal fat (54% versus 9% in men), obesity (11% versus 8% in men), and lower levels of desirable highdensity lipoprotein-cholesterol (HDL-C), which is protective against atherosclerosis (5% versus 10% in men) [6]. Unhealthy lifestyle practices among these women, such as the high consumption of readily available low-nutrient, energy dense meals and physical inactivity [6, 7], contribute to their high rates of NCDs.

Adequate levels of physical activity (PA) and a nutritious diet have been recognised as crucial lifestyle factors for the prevention of NCDs [8]. However, based on the National Health Survey, Singaporean women aged over 50 years reported: (1) high levels of leisure time physical inactivity (72%), (2) low levels of regular exercise (16%) and (3) do not meet the recommended levels of PA for health benefit (39%) [6]. Reasons for low levels of participation include: a lack of time due to work and child commitments (47%); perception of doing adequate PA from undertaking housework (23%); and a lack of interest (16%) [6]. Results from the 2010 Singaporean National Nutrition Survey also revealed that a high proportion of Singaporean women aged 50–69 years have macronutrients intake exceeding the Recommended Dietary Allowance (RDA) for energy (58%), total fat (57%), saturated fat (67%), carbohydrate (54%) and protein (71%); but only 62% of them met the RDA for dietary fibre intake [7]. In addition, a lower percentage of these women met the recommended serving guidelines for vegetables (26%), fruits (34%), wholegrains (43%) and fare only slightly better for rice and alternatives (50%) as well as the meat and alternatives food groups (51%) [7].

Most Singaporeans (> 80%), including older adults, reside with their families in dense, affordable public housing [9]. Recreational centers (RCs) are built within this public housing to provide a venue for residents to come together with the intention of fostering community cohesiveness [10]. These RCs are in close proximity and easily accessed, providing an ideal setting to reach the target group and implement and evaluate a community-based PA and nutrition intervention for older women.

Despite the evidence that healthy lifestyle behaviours are linked to a reduction in NCDs [11], limited community-based intervention research has been undertaken in the over-50s target group in Asian communities [12]. The findings reported in the academic literature on the effectiveness of the PA and nutrition strategies in community-based interventions typically originate from Canada, US, Europe and Australia. For example, a systematic review of 17 community-based interventions indicated that PA and nutrition interventions incorporating face-to-face counselling and group session modes of delivery were most effective in a community-based setting [13]. Another review of nine randomised controlled trials (RCTs) reported that nutrition counselling involving active participation in health planning, goal setting, self-efficacy and collaboration were effective in influencing positive nutrition outcomes for older adults [14], while face-to-face meetings were found to be effective [15] due to the relationships that form during the exchange of information [16]. Significant improvement in dietary behaviour and PA levels has been observed in recent health interventions targeting older healthy adults in Asia using Social Cognitive Theory (SCT) [17-19]. Furthermore, a systematic review of SCT in interventions confirmed that it provided a practical and adequate theoretical framework for guiding early phases of intervention development for chronic health conditions [20]. Therefore, the proposed cluster RCT of SCT-based PA and nutrition intervention aims to develop and implement a culturally appropriate intervention to reduce the risk factors associated with NCDs for women aged 50 years and above who utilise RCs. It is hypothesised that levels of PA and dietary behaviours, lipid profiles and fasting blood glucose (BG) levels, as well as anthropometric measures, will demonstrate statistically significant improvements in the intervention group, when compared with the control group after the 6-month intervention.

## Methods

### Study design

A 6-month, community-based PA and nutrition cluster RCT suited to the Singaporean context will be implemented and evaluated over two time points (baseline and 6 months); see Table 1. A proposed schedule for enrolment, intervention and assessment is shown in the Standard Protocol Items: Recommendations for Interventional Trials (SPIRIT) Figure (Fig. 1) and recommended items to address for intervention trials are reflected in the Additional file 1: SPIRIT Checklist [21]. A flow chart of the research procedure is displayed in Fig. 2.

**Table 1 Tab1:** Proposed pre-post data collection and intervention

**Study group**	**(Baseline) 0 month**	**Intervention**	**(Post intervention) 6 months**
Controls (*n* = 300)	O1		O2
Interventions (*n* = 300)	O1	X	O2

*O* observation, *X* intervention

**Fig. 1 Fig1:**
[figure not shown]
Standard Protocol Items: Recommendations for Interventional Trials (SPIRIT) Figure: proposed schedule for enrolment, intervention and assessment. *BG* blood glucose, *BMI* Body Mass Index, *BP* blood pressure, *PA* physical activity, *QOL* quality of life

**Fig. 2 Fig2:**
[figure not shown]
Flow chart of the research procedure. *NE* North East, *NW* North West, *RC* recreational centre, *SE* South East, *SW* South West

### Study procedure

#### Recruitment of RCs

Singapore is divided into five geographical districts, as seen in Additional file 2 [22, 23], which are all similar in terms of socioeconomic status [24]. To enhance the chance of recruiting participants into the intervention programme, three out of the five districts were randomly allocated to the intervention cluster (by drawing names from a bag) and the remaining two districts to the control cluster. The process resulted in the intervention sites (districts: 2-North West, 3-Central, and 5-South East) and control sites (districts: 1-South West, and 4-North East). Sixty RCs (intervention *n* = 30, control *n* = 30) will be randomly selected from these geographical districts. Due to the differences in the number of RCs within the districts, approximately 9–12% of the listed RCs in each district will be chosen using computer-generated random numbers. These RCs will have a minimum separation distance of 4 km to avoid risk of contamination between intervention and control groups. The recruitment process will continue until 30 control and 30 intervention RCs consent to take part in the study. The participants will all be blinded to their group status (intervention and control) during the recruitment and intervention period.

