#### Sample size determination

The power calculations are based on a logistic mixed regression model with the prevalence of moderate intensity PA participation as the outcome variable. An appropriate sample size for this study is determined in a similar manner to previous studies which examined effective recruitment and retention of older adults in a PA programme [30]; PA and nutrition intervention for seniors [31]; as well as PA and nutrition intervention targeting middle-aged adults [32]. For the mixed regression analyses when adjusting for the clustering of RCs, a sample size of *n* = 480 participants (240 participants per group) will allow for an 80% statistical power to detect a medium effect size of 10% improvement in PA prevalence (sufficient leisure time PA estimated to be 28% at baseline) [6] by the intervention group relative to the control group at a significance level of 5%. To account for a 20% attrition rate between the two time points (pre and post intervention), a total of *n* = 600 adult women will be initially recruited at baseline. The sample size takes non-respondents into consideration within the duration of the study but without covariate adjustment.

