### Statistical analysis

After data collection, outcome variables of interest, such as blood profiles, self-reported PA and dietary behaviours, and anthropometric measures will be examined and compared between subgroups of interest via the Statistical Package for the Social Science version 24 [70]. Descriptive and summary statistics will be used to quantify participants’ characteristics and outcome variables. Non-parametric statistics will be applied whenever non-normality of the outcomes is detected. Multi-variable mixed regression analyses will be used to confirm the effects of the proposed intervention, taking into account the repeated measures (at two time points) and the clustering of the observations. All variables will be entered using the stepwise regression. The regression model will also account for effects of potential confounders (age, ethnicity, education, marital status, consumption of medication and housing type).

All qualitative data from process evaluation will be transcribed, with at least 10% of all transcribed data randomly selected and reviewed for each transcription. Transcribed data will be coded to create common themes or categories. Data will be collated, presented thematically and supported by direct quotes from participants. Data management of full transcripts and other texts will be facilitated by the NVivo software package [71] to conduct a framework analysis [72, 73]. Participants will not be identified in any transcription.

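### Five districts (3 v 2) were randomised, but the abstract says 60 centres were, and the 80% power claim allows only for clustering by centre

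*Protocol article*

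**What the plan says.** Recruitment of RCs (Methods) describes the allocation: "three out of the five districts were randomly allocated to the intervention cluster (by drawing names from a bag"). Both districts left over became control. The result is already known: North West, Central and South East are intervention; South West and North East are control. The 60 RCs "will be randomly selected from these geographical districts", so what is random about an RC is whether it is sampled, not its arm.

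The abstract describes a different design: "Sixty RCs located in Singapore will be selected from five major geographical districts and randomly allocated to the intervention" (30 RCs) or control (30 RCs).

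Sample size determination names one cluster level, the RC: "For the mixed regression analyses when adjusting for the clustering of RCs", 240 women per group are said to give 80% power at a 5% significance level for a 10-point gain over 28%. No ICC or design effect is given at either level.

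Statistical analysis says the mixed regression works by "taking into account the repeated measures (at two time points) and the clustering of the observations". It names no cluster level. Its adjustment list, "potential confounders (age, ethnicity, education, marital status, consumption of medication and housing type"), does not include district. The only remark on district comparability is that the five districts are ones "which are all similar in terms of socioeconomic status".

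**The concern.** The two accounts of the allocation cannot both be right. A reader of the abstract expects 60 randomised units; the Methods show five.

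This matters because every RC in a district has the same arm by construction. A district effect shared by the women in one district therefore enters the arm comparison directly, and averaging over many RCs in that district does not reduce it. An RC random effect captures variation between RCs but largely misses variation between districts. District cannot be added as a fixed effect either, because it is aliased with arm. At stake are the standard error and p-value of each between-arm comparison, the power claim, and how strongly the trial can attribute a difference to the intervention.

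**Working it through.** **Inputs from the protocol article.** Districts: 3 intervention, 2 control. RCs: 30 per arm. Evaluable women: 240 per arm, so 240/30 = 8 per RC. Prevalence 28% v 38%, mean 33%, so v = 0.33 × 0.67 = 0.2211. Alpha 5%, taken as two-sided because the text does not say.

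**Assumptions.** District ICC (rD) 0 to 0.02 and RC ICC (rR) 0 to 0.05, since none is given. RCs split evenly within each arm (10/10/10 and 15/15). A post-only comparison on the risk-difference scale.

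**1. The plan's own figure.** The usual two-proportion formula (pooled variance under the null) for 28% v 38% at 80% power needs 346 per arm before any clustering. With 240 per arm, power is about 64%. So 80% is not reproduced even for individually randomised women. The attrition step is right: 480/0.8 = 600.

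**2. Randomisation test by district.** The number of ways to choose 2 control districts from 5 is C(5,2) = 10. The smallest possible p-value is 1/10 = 0.10. This uses no ICC.

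**3. Power with district as the unit.** Five district values leave 5 − 2 = 3 df, critical t = 3.18. The variance of the difference between arms is

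V = v[2(1 − rR − rD)/240 + 2rR/30 + rD(1/3 + 1/2)].

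The best case has both ICCs at zero: V = 0.2211 × 2/240 = 0.00184, SE 0.0429, noncentrality 0.10/0.0429 = 2.33, power about 37%. With rR = 0.01, power is about 35%, 26%, 21% and 16% at rD = 0, 0.005, 0.01 and 0.02.

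**4. Type I error of a test that uses only RC clustering.** Such a test estimates its variance from the spread of RC means within each arm. With 58 df its expected value is

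W = v(2/30)[(1 − rR − rD)/8 + rR + rD × 35/58],

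where 35 = 30(1 − 1/3) + 30(1 − 1/2) is the share of district variance visible within arms. The true error is about P(|t58| > 2.002/√(V/W)).

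Example, rR = rD = 0.01:
- V = 0.2211 × (0.00817 + 0.00067 + 0.00833) = 0.00380.
- W = 0.2211 × (2/30) × (0.1225 + 0.01 + 0.00603) = 0.00204.
- V/W = 1.86, and 2.002/1.364 = 1.47, so the error is about 15%.

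Over rR from 0 to 0.05:

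| District ICC | True type I error (nominal 5%) |
|---|---|
| 0 | 5% |
| 0.001 | about 6% |
| 0.005 | 9-10% |
| 0.01 | 13-15% |
| 0.02 | 20-23% |

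Simulation of RC-level t-tests agrees with these values to within about half a percentage point.

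**The case against.** Four points can be made for the plan, and each limits the claim.

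- **The harm is conditional.** A reader might infer that the type I error certainly exceeds 5%. The documents do not support that: no district ICC is given, and at zero the RC-level test is nominal. The authors do offer a reason to expect little variation, the similarity in socioeconomic status. That is one characteristic, however, and it does not establish zero between-district variance in activity, diet, lipids or glucose.
- **Baseline is measured.** A reader might also infer that any difference between the two sets of districts would count as treatment effect. If the test is of change from baseline to 6 months, stable differences cancel and only differing change remains. Restricting entry to women below 150 minutes of moderate leisure activity a week may also narrow baseline differences. The error rates above are for a post-only comparison and need not carry over to change. Baseline data add no randomised units, so the 0.10 floor is unaffected.
- **The analysis section names no cluster level.** It would go too far to say that section specifies an RC-only model; the random-effects structure may be set out elsewhere. The firm text is in the sample-size section, which ties its mixed regression to RC clustering. District appears in neither.
- **The term cluster RCT is not false.** It also fits allocation by district. The false statement is the abstract's account of which unit was allocated.

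It may also be tempting to propose randomising the remaining RCs within districts because recruitment continues. Trial status reports only participant recruitment as ongoing and does not say that any RC is still unapproached. Changing course now would mix two allocation schemes and put both arms in one district.

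**Conclusion.** The point stands in conditional form. Three parts need no assumption about the ICC. The abstract and the Methods contradict each other on the allocated unit. The power statement refers to a unit that was not the one randomised. With 10 possible allocations, no district-level randomisation test can reach 5%.

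Power on 3 df is at most about 37% for 28% v 38% with 240 per arm. That shortfall from 80% is not all due to district: the separate fact that 240 per arm gives about 64% unclustered accounts for part of it, and the few degrees of freedom for the rest.

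The inflated type I error depends on between-district variance above zero, in the outcome or in its change. It ranges from negligible (about 6% at an assumed ICC of 0.001) to serious (20-23% at 0.02), and the documents cannot place the trial within that range. This should be corrected before analysis, because it affects the between-arm p-values and the description of the randomisation itself.

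**What to change.** 1. Correct the abstract and the sample-size text to say that five districts were allocated 3 v 2 and RCs were sampled within them, and that the 80% power figure does not apply to that unit.
2. Put district in the error term: women within RC within district, with arm tested on 3 df. Alternatively, compare district-level summaries of change and give a permutation p-value, noting its floor of 0.10.
3. Keep the RC-only mixed model as a sensitivity analysis, labelled as assuming zero between-district variance.
4. Report the effect as an estimate with a confidence interval, and qualify the causal claim on the ground that five districts were randomised.

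The cost is wording and analysis specification; no new data are needed. The price is less favourable stated precision. Analysis cannot fully rescue the design, because no model adds randomised units.

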#### Recruitment of participants

A sample of 600 (interventions *n* = 300; controls *n* = 300) women will then be recruited from these 60 RCs. Participants are required to be: (1) female, aged 50 years and above, (2) undertaking less than 150 min of moderate intensity leisure PA per week (self-reported), (3) not have any medical condition that prohibits involvement in a PA programme, and (4) not currently enrolled in other nutrition and PA research studies.

#### Procedure

Programme recruitment flyers will be placed on the RC’s bulletin boards and promoted by the RC managers. Those residents indicating to the RC managers that they are interested in the programme and agreeing to provide their contact details will have their telephone number provided to the research team. These participants will then be telephoned to explain the purpose of the study and to determine their eligibility based on the selection criteria. After the initial telephone screening, eligible participants will be invited to take part, informed of their rights and confidentiality issues, and that they are free to withdraw at any stage.

At the initial meeting, baseline data will be collected and recorded using the health surveys available in the English and Chinese language reflected in the Additional files 3 and 4 [25-27]. Trained researchers (final-year tertiary students) will collect self-reported data on dietary habits and PA levels used to assess current dietary and PA levels and undertake anthropometric measures. These programme ambassadors are final-year nutrition, sports and wellness undergraduate students who will conduct their activities under close supervision of qualified nutritionists and certified fitness instructors. The principal investigator (PI) will fit and explain the management of the accelerometers. Fasting blood samples will be collected by a phlebotomist. Any participants exhibiting hypercholesterolaemia (total cholesterol (TC) ≥ 6.2 mmol/L) [28] or hyperglycaemia (BG > 7 mmol/L) levels [29] will be excluded from the study and referred to their medical practitioner for follow-up. Participants on medication will not be excluded and both the pre and post survey will document all those who are on medication including the type of medication and subgroup analysis will be undertaken.

Both the intervention and control participants who undergo pre and post data collection will be given an incentive of free health products (health calendar, sports towel, writing pad and pen with health messages) and supermarket vouchers in appreciation of their involvement in the study. However, the control group will be blinded to the nature of the intervention and instead only receive a falls prevention booklet.

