### Intervention

This 6-month community-based Singapore Physical Activity and Nutrition Study (SPANS) intervention programme will be based on the Singaporean PA and nutrition guidelines [66-68]. Programme ambassadors will undergo comprehensive training in MI and intervention programme and will undertake all the intervention activities and distribute the resources bi-weekly (see Table 4).

**Table 4: Tab4:** Singapore Physical Activity and Nutrition Study (SPANS) intervention

**Session (timing)**	**Session details**	**Participant’s resources / interactive activities**
**PA sessions** **(1 hr- twice a month)** **[Week 2 -24]**	1. Introduction to SPANS programme 2. **Focus PA:** aerobic • Benefits/barriers/motivators • Guidelines 3. Establish short and long term PA goals	1. **Resources** • ‘Active for Life’ booklet 2. **Interactive activities** • PA warm up • Muscle strengthening and low intensity aerobic workout • Cool down and stretches
**Nutrition session 1 – Eat Well, Live Well** **[Week 1]**	1. **Focus on nutrition** • Benefits/barriers/motivators • Healthy plate model and guidelines 2. Establish short and long term nutrition goals	1. **Resources:** • ‘Nutrition Guide for Healthy Aging’ booklet • Health calendar with monthly recipes and health tips 2. **Interactive activities:** • What’s On Your Plate? • Read your food label
**Nutrition session 2 – Smart Shopping and Dining Alert [Week 12]**	1. **Focus on nutrition** • Healthy shopping and cooking tips • Healthier Choice Symbols	1. **Resources** • ‘Recipes for Health Aging’ booklet • ‘Lowering BP’ booklet 2. **Interactive activities** • Ranking game on food calorie • Guess the herbs and spices in cooking
**Nutrition session 3 – Take Charge Of Your Health** **[Week 24]**	1. **Focus on nutrition and PA** • Manage cholesterol and BG levels 2. Identify social support and overcome relapse	1. **Resources** • ‘Keeping Cholesterol in Check’ booklet • ‘Tips to Better Health: Keeping My Blood Sugar Levels Healthy’ booklet 2. **Interactive activities** • Mix and match cholesterol in foods • Brainstorm on improving BG levels

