#### Group PA, nutrition talks, dietary counselling sessions and telephone contact

Bi-weekly, low-intensity PA, strength and balanced exercises sessions will be conducted. There will be bimonthly nutrition talks, bimonthly dietary counselling and monthly follow-up calls incorporating MI. Programme ambassadors will follow-up with participants’ enquires and provide feedback to support the adoption of healthy practices and monitor the progress of their participants’ goals. Participants will be encouraged to do moderate intensity PA for at least 150 min per week and reminded to monitor their daily progress and goals by recording the frequency and duration of PA in a health calendar provided at the commencement of the programme. Goal setting and feedback will be emphasized at all contact points during the intervention.

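### The students named as collectors of self-reported activity and diet are also the programme ambassadors who coach the intervention arm, and the statement that all participants are blinded cannot hold

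*Protocol article*

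**What the plan says.** **Who collects the data.** In the Procedure section, within the paragraph on the initial meeting: "Trained researchers (final-year tertiary students) will collect self-reported data on dietary habits and PA levels". The same students also take the anthropometric measures. The next sentence names them: "These programme ambassadors are final-year nutrition, sports and wellness undergraduate students who will conduct their activities under close supervision".

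**Who delivers the programme.** Under Intervention, the programme ambassadors are trained in motivational interviewing and "will undertake all the intervention activities and distribute the resources bi-weekly". The section on group sessions and telephone contact adds that they "provide feedback to support the adoption of healthy practices and monitor the progress of their participants’ goals", and sets intervention women a weekly target of 150 minutes of moderate activity.

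**Who the ambassadors are.** The Abstract (Background) describes them differently, as certified fitness instructors and nutritionists. In the Procedure section such staff only supervise them.

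**Blinding.** Recruitment of RCs: "The participants will all be blinded to their group status (intervention and control) during the recruitment and intervention period". Procedure: "the control group will be blinded to the nature of the intervention and instead only receive a falls prevention booklet". Procedure also says of interested residents: "These participants will then be telephoned to explain the purpose of the study".

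**Outcomes.** Table 2 lists four primary domains: self-reported activity (GPAQ), accelerometry, self-reported diet (STEPS questionnaire) and fasting bloods. The sample size rests on the prevalence of moderate-intensity activity.

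**The concern.** Two of the four primary domains are what a woman says she did. In the intervention arm she will have spent six months with ambassadors who set goals with her, reviewed them and taught her the target. In the control arm she will have had a falls prevention booklet. If the same pool of ambassadors takes the 6-month reports, the pull towards a pleasing answer is likely to be stronger in the intervention arm, and it points towards benefit. The mixed model and the confounder adjustment in the Statistical analysis section cannot remove a reporting difference that coincides with the treatment arm.

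The blinding sentence is a separate fault. It asserts a protection that the design cannot give. If it is carried into the trial report, readers will misjudge the risk of bias in the self-reported outcomes.

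**Working it through.** The plan gives no figure on this point, so there is none to reproduce. The check is a comparison of the text, followed by an illustration.

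**1. Dual role.**
- Procedure: the collectors are final-year students, and "These programme ambassadors are final-year nutrition, sports and wellness undergraduate students".
- Intervention: the ambassadors carry out all activities.
- Together these make the named collectors and the coaches one group.
- The collector sentence describes baseline, when no coaching has yet taken place. The article names nobody else for 6 months. The overlap at follow-up is therefore an inference from the only collector named.
- Programme contact runs to week 24 (Table 4), next to the 6-month assessment, and the STEPS questionnaire asks about the past week.

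**2. Blinding.**
- The broad statement covers all participants, their group status, and the intervention period.
- Intervention women attend exercise sessions, nutrition talks and counselling and receive monthly calls, after being told the purpose of the study by telephone. They cannot be unaware of what they receive.
- The narrower statement covers only controls, and only the nature of the intervention. That is a different and more defensible claim, and the broad sentence goes beyond it.

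**3. Illustration of size.** Inputs from Sample size determination: 28% sufficiently active at baseline, 240 evaluable per group, 5% significance. Assumptions: two-sided test (sidedness is not stated), no true effect, the outcome taken as self-reported, and over-reporting that raises the measured intervention prevalence by *b* relative to control.

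With p1 = 0.28, p2 = 0.28 + b, p̄ = (p1 + p2)/2 and n = 240:
- SE0 = √[2p̄(1 − p̄)/n]
- SE1 = √[(p1(1 − p1) + p2(1 − p2))/n]
- P(reject) = Φ[(b − 1.96·SE0)/SE1] + Φ[(−b − 1.96·SE0)/SE1]

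For b = 0.05:
- p̄ = 0.305
- SE0 = √(2 × 0.305 × 0.695/240) = 0.0420
- SE1 = √[(0.28 × 0.72 + 0.33 × 0.67)/240] = 0.0420
- First term: Φ(−0.77) ≈ 0.220. Second term: about 0.001. Total: 22.1%.

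The share of insufficiently active women who would have to be recorded as active is b/0.72.

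For clustering, 240/30 = 8 women per centre, and n is divided by 1 + 7 × ICC. The article gives no ICC, so 0.01 and 0.05 are assumed; the divisors are 1.07 and 1.35.

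| Assumed b | Share of inactive women misreported | Unclustered | ICC 0.01 | ICC 0.05 |
|---|---|---|---|---|
| 2 points | 2.8% | 7.7% | 7.5% | 7.0% |
| 3 points | 4.2% | 11.1% | 10.7% | 9.5% |
| 5 points | 6.9% | 22.1% | 21.0% | 17.6% |
| 10 points | 13.9% | 64.5% | 61.6% | 51.8% |

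A 10-point bias equals the whole effect that the trial is powered to detect.

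**The case against.** The strongest reply is that the collector sentence concerns baseline. Nothing says that a woman will report at 6 months to the person who set her goals, and a condensed article may leave follow-up staffing to the full protocol. That stands as a limit: the overlap at follow-up is what the text implies, not what it states.

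Second, the Abstract's description of the ambassadors as certified professionals makes the overlap less certain. This also stands. The two descriptions conflict and must be reconciled. The blinding sentence fails under either.

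Third, several stronger readings are tempting and the article does not support them.
- A reader might infer that desirable reporting occurs in the intervention arm only. Controls also learn the purpose and report to study staff, so only a difference between arms is plausible.
- A reader might infer that accelerometry has no control data. The Accelerometers section does describe fitting to intervention participants, but the Abstract's hypothesis and Table 2 treat objective activity as a between-group outcome. That is a contradiction to resolve separately, not proof that control data are absent.
- A reader might assume that the surveys are interviews. The mode is not stated, and self-completion may already be in use.

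Fourth, coached women who know their arm may over-report to anyone. This is correct: separating coach from collector removes only part of the bias, and the size of that part is unknown.

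**Conclusion.** The point holds in this form. As written, the only named collectors of the GPAQ and STEPS data are the staff who deliver the programme, so two of the four primary domains are open to differential reporting in the direction of benefit. The follow-up overlap is an inference, and it depends on the Procedure section's account of the ambassadors rather than the Abstract's.

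The blinding sentence is wrong as it stands and needs no inference.

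The false-positive rates, about 8%, 11%, 22% and 65% for 2, 3, 5 and 10 points (about 18–21% for 5 points with an ICC of 0.05–0.01), show sensitivity to an assumed bias. A reader might take 22% as this trial's expected error rate. The documents give no estimate of over-reporting, so that reading is unsupported. Fasting bloods are not self-reported and are outside the reporting concern.

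**What to change.** 1. Schedule the existing students so that none collects 6-month questionnaires or measurements at a centre where that student delivers sessions. Have women complete the English or Chinese surveys themselves where possible. This separates coach from assessor but does not fully mask the arm: whole districts were allocated, so a student who delivers sessions can infer a centre's arm from its location. The cost is scheduling and some travel.
2. State who collects the 6-month data, and reconcile the Abstract and Procedure descriptions of the programme ambassadors. The cost is wording.
3. Replace the blinding sentence in Recruitment of RCs with: *Participants are not blinded to the activities they receive. Control participants are not told the content of the intervention.* Add that laboratory staff are masked only if that is in place; the Blood samples section does not say so. The cost is wording.

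Recruitment was still under way at submission (Trial status), so at that stage the 6-month scheduling could still be arranged for women yet to reach follow-up.
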